## Abstract

**Background:**

Stroke is a global societal challenge. Annually, 13 million people experience stroke, and the prevalence of stroke is increasing in low-income countries; hence, accessible rehabilitation needs to be developed. Information and communication technology can help by providing access to rehabilitation support through information, self-evaluation, and self-management of rehabilitation. The F@ce 2.0 rehabilitation program provides support in goal-setting and problem-solving strategies through phone calls from the interventionist twice a week and daily SMS text message reminders over 8 weeks to improve performance in valued activities in everyday life. Our hypothesis is that F@ce 2.0 will increase functioning in daily activities and participation in everyday life as well as improve performance and satisfaction in valued daily activities and self-efficacy (ie, confidence in own ability to perform activities) among people living with the consequences of stroke.

**Objective:**

This study aims to implement F@ce 2.0, a mobile phone–supported and family-centered rehabilitation program, and evaluate its effects on performance in daily activities and participation in everyday life in comparison to ordinary rehabilitation among persons with stroke and their family members in Uganda. An additional aim is to explore experiences of participating in F@ce 2.0 and plausible mechanisms of impact that might explain the potential effects of F@ce 2.0.

**Methods:**

A randomized controlled trial will be conducted to compare the outcomes of the F@ce 2.0 group and a control group receiving ordinary rehabilitation. Health care professionals will recruit 90 clients from both urban and rural areas. The primary outcomes for persons with stroke are perceived performance in daily activities assessed using the Canadian Occupational Performance Measure and self-efficacy assessed using the Self-Efficacy Scale; for family members, the primary outcome is caregiver burden evaluated using the Caregiver Burden Scale. Descriptive statistics will be used to present characteristics and outcomes at 3 and 6 months. All statistical analyses comparing the outcomes at the different time points between the F@ce 2.0 and control groups will be performed using intention-to-treat analysis. Qualitative interviews will be used to explore the experiences of persons with stroke and their family members participating in F@ce 2.0, using a grounded theory approach to data collection and analysis. A process evaluation will be conducted using a single-case study design with mixed methods to explore the implementation process.

**Results:**

Recruitment and data collection in the randomized controlled trial were initiated in January 2022 and have been completed. The intervention has been provided to 51 participants in the intervention group. Interviews of persons with stroke, family members, and health care professionals have been conducted. Data analysis will be performed during autumn 2024 and spring 2025.

**Conclusions:**

This study will provide evidence of the plausible effects of F@ce 2.0 and the process of implementing the program in low-income countries.

**International Registered Report Identifier (IRRID):**

DERR1-10.2196/60955

## Introduction

### Background

The point of departure for this study is that all people living with a disability and their families have needs and the right to participate and engage in everyday life. Social participation [1] and engagement in daily activities [2] are strongly associated with health and well-being [3]. Everyday life changes often occur for people with stroke and their families [4], and there is a need for rehabilitation and support to enable functioning in daily activities and social participation in the community.

Stroke is a noncommunicable disease and a global societal challenge according to the World Health Organization [5]. Annually, >13 million people experience stroke, which means that worldwide 1 in 4 people aged >25 years will have stroke in their lifetime, and one-third will subsequently live with remaining disabilities [6]. The burden of stroke is increasing substantially in Africa [7,8], which has some of the highest incidence rates in the world [9]. Stroke currently ranks as the sixth leading cause of mortality in Uganda [10].

Empirical studies on the effectiveness of rehabilitation after stroke have shown positive effects of activities of daily living (ADLs) interventions [11]. However, most research and evidence for beneficial rehabilitation interventions after stroke originates from high-income countries, and evidence is lacking that such interventions can be implemented with similar outcomes in the context of sub-Saharan Africa [8]. In 2021 in Uganda, 41% of the population was living below the poverty line, subsisting on the equivalent of US $1.90 per day [12]. Furthermore, the majority of the Ugandan population (74%) lived in rural areas, where medical rehabilitation was almost nonexistent [13]. In addition to the poor socioeconomic conditions in Uganda, access to rehabilitation services can be limited due to poor infrastructure, inadequate numbers of rehabilitation professionals, and poor health support systems.

To increase accessibility to rehabilitation services, the development and implementation of contextually appropriate rehabilitation programs is urgently needed. One way to increase accessibility to rehabilitation could be to use the knowledge of health care professionals (HCPs) to train village health workers, who in turn can provide rehabilitation support in agreement with the model for community-based rehabilitation (CBR) [14]. The CBR model respects diversity and aims to empower people with disabilities and reduce stigma against them; it is also in line with a client- and family-centered approach.

In addition to causing disabilities, stroke can lead to a stressful situation for family members, with risk for depression, perceived caregiver burden [15], social isolation, physical problems, and decreased life satisfaction [16]. In Uganda, families are commonly involved after stroke and take responsibility for care not only in the acute hospital setting but also in community living [17]. Rehabilitation programs after stroke should therefore involve family members to attain common goals for rehabilitation, such as participation in ADLs [18].

In our previous research [19], our findings stressed that it was important that people with stroke had “significant experiences that contributed to change” by performing activities they wanted and appreciated during their rehabilitation process. Therefore, activities that are relevant and valued for people in everyday life can be used as goals to improve ADL functioning [20]. Furthermore, if the people succeed in performing activities of their choice, their confidence in their capability to perform activities will be strengthened (ie, increased sense of self-efficacy) [21,22]. In our previous qualitative studies, the importance of including the client’s perspective as the point of departure for interventions has been expressed by persons with stroke as well as by HCPs [23,24]. Moreover, family support and engaging activities were described as increasing participation and functioning in everyday life [19]. The rehabilitation program F@ce 2.0 is therefore family-centered, that is, it includes both the person with stroke and his or her family members, which is in line with client-centered practice [25,26].

Mobile phones are part of information and communication technology (ICT), that is, according to the United Nations Educational, Scientific and Cultural Organization, they are “forms of technology that are used to transmit, process, store, create, display, share or exchange information by electronic means” [27]. Mobile phones have rapidly become an integral part of everyday living for people in sub-Saharan Africa and are often the sole means of communication with those living outside urban areas. According to The Mobile Economy Sub-Saharan Africa 2020 report, mobile services are predicted to continue growing in the region at an annual rate of 4.3% until 2025 [28]. Mobile phones have the potential to extend the reach of health care and rehabilitation [29] with an impact on the United Nations’ Sustainable Development Goal 3 [30], which seeks to ensure healthy lives and promote well-being for all at all ages. It has been shown that despite having physical and cognitive impairments, people with stroke could benefit from using mobile phone technology in their daily lives [31]. In addition, our previous studies [32,33] in Uganda have shown that mobile phone technology can be used to support the rehabilitation process after stroke via follow-up calls, SMS text message reminders, and feedback on the performance of activities. However, in our feasibility study of the mobile phone–supported rehabilitation program F@ce 1.0 [33], participants were recruited from an urban area, and the sample size was not powered to draw conclusions about the effects. Furthermore, F@ce 1.0 has been developed into an interdisciplinary intervention, F@ce 2.0 [34]. Hence, F@ce 2.0, which includes (1) educational workshops for the assigned HCPs, (2) a goal-directed and mobile phone–supported intervention, and (3) a web-based platform providing daily SMS text message reminders to patients, will be evaluated in a larger trial.

### Objectives

The overall aim of this project is to implement F@ce 2.0, a mobile phone–supported and family-centered rehabilitation program, and evaluate its effects on performance in daily activities and participation in everyday life in comparison to ordinary rehabilitation among persons with stroke and their family members. An additional aim is to explore the experiences of participating in F@ce 2.0 and plausible mechanisms of impact that might explain the potential effects of using F@ce 2.0 by studying the implementation process in both urban (Kampala, the capital city) and rural (Greater Masaka) areas.

Our hypothesis is that persons with stroke who participate in the F@ce 2.0 intervention will increase their functioning in daily activities and participation in everyday life as well as perceive their performance and satisfaction in daily activities and their self-efficacy to be higher than those receiving ordinary rehabilitation.

### Research Questions

We developed the following research questions (RQs):

RQ 1: Are there any differences in effects after the 8-week intervention and at follow-up at 6 months between people with stroke who participated in F@ce 2.0 and those who received ordinary rehabilitation with regard to perceived performance in daily activities, self-efficacy, participation in everyday life, and independence in ADLs?RQ 2: Are there any differences after the 8-week intervention and at follow-up at 6 months between the family members of those receiving the F@ce 2.0 intervention in comparison to the family members of those receiving ordinary rehabilitation regarding caregiver burden and life satisfaction?RQ 3: How do the persons with stroke and their family members experience their participation in F@ce 2.0?RQ 4: How can the outcomes of F@ce 2.0 be understood and explained when considering the implementation process and the plausible potential mechanisms of impact?

## Methods

### Study Design

A randomized controlled trial with a pretest-posttest parallel design with an intervention group (IG) and a control group (CG) has been chosen to compare outcomes between participants receiving F@ce 2.0 (IG) and those receiving ordinary rehabilitation (CG). The study follows the Medical Research Council’s guidance [35] for evaluating complex interventions; hence, the study uses both quantitative and qualitative methodologies and a process evaluation. The trial will be monitored according to the CONSORT (Consolidated Standards of Reporting Trials) 2010 statement for nonpharmacological trials [36] and the CONSORT 2010 extension for pragmatic trials in health care [37]. Furthermore, this protocol adheres to the SPIRIT (Standard Protocol Items: Recommendations for Interventional Trials) 2013 statement [38,39]. The study has been registered at ClincialTrials.gov (NCT04337034).

### Study Setting

The F@ce 2.0 program will be implemented in 2 designated geographic areas in Uganda: Kampala (representing an urban area) and Greater Masaka (a rural area). Rehabilitation professionals or HCPs working at health care centers and CBR centers in these 2 geographic areas will be recruited to provide the F@ce 2.0 intervention or the ordinary rehabilitation intervention. These centers are funded either publicly or privately [40]. Staff numbers vary at these centers, and the recruitment of HCPs will differ depending on which types of professionals are employed. Preference will be given to occupational therapists, physiotherapists, and nurses, but other professionals might also be approached. HCPs assigned to deliver the F@ce 2.0 intervention will participate in educational workshops provided by the research group to prepare for delivering the intervention to the IG participants.

### Eligibility Criteria

Persons with stroke, family members of the persons with stroke, and HCPs working at the participating centers will be eligible to participate.

Persons with stroke will be included if the following criteria are fulfilled: (1) stroke diagnosis confirmed by computer tomography scan or by clinical symptoms; (2) enrolled at 1 of the 3 participating centers; (3) aged >18 years; (4) having no psychiatric diagnosis; (5) able to understand and formulate activity goals in English or Luganda; (6) access to, and self-reported ability to use, a mobile phone; and (7) a modified Rankin Scale level ranging from 2 to 4, indicating a slight to moderately severe disability [41].

A family member, identified as close to the person with stroke (ie, wife, husband, friend, daughter, neighbor, etc) and chosen by the person with stroke, will also be invited to participate.

### The F@ce 2.0 Program in the Ugandan Context

#### Workshops for Intervention Providers

The HCPs (ie, occupational therapists, physiotherapists, and nurses; n=4) assigned to deliver the intervention in the Kampala and Greater Masaka areas will participate in preparatory training workshops. The workshops will be organized on 2 days in 1 week as face-to-face seminars led by the research team. During the workshop sessions, the empirical and theoretical underpinnings of F@ce 2.0 will be presented and discussed. Further relevant issues regarding rehabilitation after stroke will be reflected on and discussed between the HCPs and the researchers. Furthermore, the use of ICT as a tool within rehabilitation will be initiated, discussed, and practiced during the workshop [33]. Finally, ways to integrate the F@ce 2.0 intervention into ordinary rehabilitation will be considered with the HCPs, and client cases will be used and elaborated on to facilitate their reflective learning process.

#### The F@ce 2.0 Intervention

The 8-week mobile phone–supported and family-centered intervention aims to increase functioning in daily activities for persons living with the consequences of stroke and participation in everyday life for persons with stroke and their family members. Using the Canadian Occupational Performance Measure (COPM) [42], the person with stroke formulates 3 *targets* (goals) in daily activities that they want and need to perform in the home environment. The participant, together with an identified family member, will be introduced to a problem-solving strategy framed as *target-plan-perform-prove*, intended to facilitate the learning and problem-solving process. Each activity will be practiced together with the family member, and the performance will be discussed together with the HCP to identify and formulate a *plan* for overcoming the difficulties in performing the activities chosen as targets. Different strategies will be developed and formulated together with the HCP, such as finding new ways to perform the target activities and to modify the environmental demands. To enable the family member to support the person with stroke to *perform* and practice if needed, they will be informed about the participant’s target activities and the planned strategies.

#### The Web Platform and Use of the Mobile Phone in F@ce 2.0

The participants will practice the target activities in their home environment, supported via mobile phone calls and SMS text messages. The SMS text messages will be sent from a web platform (developed using Node.js/PostgreSQL for the backend and HTML/CSS/JavaScript for the front-end) [43] where the HCPs will register the participants’ target activities and strategies for the training that they have agreed on. The participants or the family members will receive individual SMS text messages containing the 3 targets twice daily, morning and evening. The morning message will remind the participants to perform the activities during the day. In the evening, the participants, with or without support from a family member, will be asked to rate (on a scale ranging from 0 to 5) their performance of the 3 target activities, where 0=*has not performed the activity* and 5=*carried out the activity well*. If participants rate their performance as 0 or do not reply to the SMS text message reminder, a red flag alert will automatically be generated on the HCP’s mobile phone. The HCP will contact the participant the following morning to find out what happened and come to an agreement regarding the next strategy. The participants receiving F@ce 2.0 will also receive mobile phone calls as a follow-up strategy from their HCP twice a week.

#### Additional Intervention for Study Participants

All participants in the study (IG+CG) will be given oral and written information about stroke during the initial assessments. Self-reported use of health services will be collected, with assistance from family members if needed. The participants in the CG will receive the health care intervention and rehabilitation provided by their center, but they will not receive any rehabilitation supported via SMS text messages.

### Outcome Data

The primary outcomes for persons with stroke are perceived performance in daily activities evaluated with the COPM [42] and self-efficacy in performing daily activities (ie, the persons’ confidence in their ability) measured using the Self-Efficacy Scale (SES) [44,45]. The secondary outcomes will be the perceived impact of stroke evaluated with the Stroke Impact Scale 3.0 (SIS 3.0; Ugandan version) [46] and independence and dependence in ADLs measured using the Barthel Index (BI) [47]. The outcomes for family members will be caregiver burden assessed with the Caregiver Burden Scale (CBS) [48] and life satisfaction assessed with the Life Satisfaction Questionnaire-11 (LiSat-11) [49].

### Participant Timeline

Participant enrollment was initiated in 2022, and the last qualitative interview was performed during spring 2023. During this period, 90 persons with stroke and their family members were enrolled in the study. HCPs from the rehabilitation teams were enrolled as participants during the F@ce 2.0 intervention and will be followed until the study is completed.

For each participant, demographic data and baseline assessments were conducted during the first week after enrollment and postintervention assessments approximately 9 weeks after enrollment (ie, within 1 week after finalizing the program).

The study timeline is presented in Table 1.

**Table 1 table1:** Participant timeline and data collection.

		Study period					
		Enrollment	Allocation	After allocation			
		Wk 0	Baseline	Intervention (wk 1-8)	Wk 9	6 mo	After last participant completes intervention
**Enrollment**							
	Eligibility screening	✓					
	Informed consent	✓					
**Interventions**							
	F@ce 2.0			✓			
	Control: rehabilitation as usual			✓			
**Assessments: persons with stroke**							
	Demographics		✓				
	SSS^a^		✓				
	Barthel Index		✓				
	Self-Efficacy Scale		✓		✓	✓	
	COPM^b^		✓		✓	✓	
	SIS 3.0^c^ (Ugandan version)		✓		✓	✓	
	Use of health care and risk factors		✓			✓	
	Qualitative interviews				✓	✓	
	Survey regarding intervention (Multimedia Appendix 1)				✓		
**Assessments: family members**							
	Demographics		✓				
	LiSat-11^d^		✓		✓	✓	
	Caregiver Burden Scale		✓		✓	✓	
	Qualitative interviews				✓	✓	
	Survey regarding intervention (Multimedia Appendix 1)				✓		
**Assessments: team members and HCPs^e^**							
	Demographics		✓				
	Team members’ and HCPs’ reflections after workshop and coaching	✓	✓				
	Team members’ and HCPs’ logbooks on follow-up calls and additional services supplied			✓			
	Qualitative interviews of HCPs on intervention process (Multimedia Appendix 2)						✓
	Registrations on the web platform			✓			
	Fidelity check^f^			✓	✓		

^a^SSS: Scandinavian Stroke Scale.

^b^COPM: Canadian Occupational Performance Measure.

^c^SIS 3.0: Stroke Impact Scale 3.0.

^d^LiSat-11: Life Satisfaction Questionnaire-11.

^e^HCP: health care professional.

^f^Conducted monthly with the whole team throughout the study.

### Sample Size and Power Considerations

A power calculation based on the results from our pilot study in Uganda [33] regarding the primary outcome—a clinically important difference of 2 points according to the COPM (ie, perceived performance and satisfaction in daily activities)—showed that 36 participants in each group are needed. Considering an attrition rate of 25%, a total of 90 participants will be required (α set at .05 and β at .80).

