## Results

As of March 2024, a total of 100 participants with stroke had been enrolled in the randomized controlled trial, of whom 2 (2%) died of natural causes. A total of 96 family members had also been enrolled. The intervention has been performed via daily reminders sent by SMS text messages and phone calls twice a week by the interventionist. Data collection was initiated on January 25, 2022. All baseline and follow-up assessments have been completed. Data analysis is planned to start in October 2024 for the randomized controlled trial and it is planned to be submitted during May 2025. Data collection for the qualitative study and the process evaluation have been completed. Data analysis for the qualitative study will be initiated in February 2025. The process evaluation has been submitted to a scientific journal.

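### The planned total of 90 allows for 20% attrition, not the stated 25% (which needs 96), and power of .80 is labelled as β

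*Protocol article*

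**What the plan says.** The protocol article, under Sample Size and Power Considerations, takes as its target "a clinically important difference of 2 points according to the COPM" and reports that the calculation, based on the pilot study, "showed that 36 participants in each group are needed". It continues: "Considering an attrition rate of 25%, a total of 90 participants will be required (α set at .05 and β at .80". The Methods part of the Abstract gives the same planned recruitment of 90.

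Two later sections report enrolment. Participant Timeline covers the time from 2022 to spring 2023 and says: "During this period, 90 persons with stroke and their family members were enrolled in the study". Results, dated March 2024, says that "a total of 100 participants with stroke had been enrolled in the randomized controlled trial". The article does not connect the two counts.

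**The concern.** Three figures in one short section do not fit together: 36 per group, 25% attrition and a total of 90. An attrition allowance should leave the required number of completers after the expected loss, and 90 does not do that at 25%. As written, the published justification misses its own target.

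The same sentence sets β at .80. β is the type II error rate, so read literally this is a design with 20% power. It is the only place where the article states the design's error rates, and a reader who takes it at face value is misinformed.

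Enrolment also went past the number described as required, and the article does not say when or why.

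**Working it through.** **Inputs.** From Sample Size and Power Considerations: 36 evaluable per group (72 in total), a difference of 2 COPM points, 25% attrition, α .05, planned total 90. From Results: 100 enrolled. The article does not give the SD or say whether the test is one- or two-sided. I assume a two-sided test, 1:1 allocation (implied by equal group sizes) and 80% power at 36 per group.

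**Reproducing the 90.** 72 × (1 + 0.25) = 90, an exact match.

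**Correct inflation.** N = n / (1 − attrition) = 72 / 0.75 = 96, or 48 per group.

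**What 90 delivers at 25% loss.** 90 × 0.75 = 67.5 completers, or 33.75 per group, which is 4.5 short of 72.

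**Attrition that 90 can absorb.** 1 − 72/90 = 20%.

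None of the steps so far depends on the SD, the sidedness or the power.

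**Implied SD (normal approximation).** SD = 2 × √(36/2) / (1.960 + 0.842) ≈ 3.03. A noncentral t calculation gives 2.99.

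**Power at the expected completers.** Power = Φ[(1.960 + 0.842) × √(n/36) − 1.960], with n per group:

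| Enrolled | Completers at 25% loss | Per group | Power |
|---|---|---|---|
| 90 | 67.5 | 33.75 | 77.4% |
| 96 | 72 | 36 | 80.0% |
| 100 | 75 | 37.5 | 81.6% |

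For 90 enrolled, the noncentral t gives 77.3%. Rounding down to 33 per group gives about 76.5%. If the test were one-sided, (1.645 + 0.842) × √(33.75/36) − 1.645 ≈ 0.763, so power would be about 78%. The loss is therefore about 2 to 4 percentage points across these readings.

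**β.** Power = 1 − β. With β = .80, power would be .20; with β = .20, power is .80. If 36 per group gave only 20% power for a 2-point difference, the same formula would imply an SD of about 7.6. Power .80 is the natural reading.

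**The case against.** The strongest reply is that the practical consequence is now small. Recruitment and follow-up are complete, the reported 100 exceeds 96, and no planned analysis changes. That stands: a reader might infer that the completed trial is underpowered because of this error, and the article does not support that.

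The power figures are also conditional. They rest on a back-solved SD and an unadjusted comparison, whereas Data Analyses plans multivariate methods with covariates. They are a guide to size and not the power of the planned analysis. The comparison of 67.5 with 72 completers is free of this limitation.

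It could be said that carrying the last value forward keeps all 90 in the analysis. It keeps the rows, but carried-forward values do not replace the completers that the allowance is meant to secure. If they did, no allowance would be needed.

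Four stronger readings are tempting and are not supported:

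- **That the β slip lowers power.** It is a label. Only the inflation step affects the number.
- **That 90 and 100 contradict each other.** They carry different dates, spring 2023 and March 2024, and both may be true.
- **That the intention-to-treat denominator is inconsistent.** Both sections give enrolment counts and neither states an analysis set. Results says enrolled, and allocation follows the baseline assessment, so it is not established that all 100 were randomised.
- **That enrolment was extended after a look at outcomes.** Nothing indicates this. The trial analysis was planned from October 2024, after all follow-up was complete, the statistician is to be blinded, and no interim analysis is described.

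The SD is not requested here either: the article names the pilot study as its source, and a condensed article may leave that detail to the full protocol.

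**Conclusion.** The arithmetic error is certain and follows from the section's own figures: 25% attrition on 72 evaluable participants requires 96, and 90 covers 20%. Assuming 80% power at 36 per group, a two-sided .05 test and 1:1 allocation, the planned 90 gives about 77% power, roughly 3 points short. This is a modest fault in the stated justification and does not carry over to the reported enrolment of 100, which under the same assumptions gives about 82%. The β entry is a separate labelling error with no effect on power. The move from 90 to 100 enrolled needs a sentence of explanation; it is not evidence of any irregularity.

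**What to change.** In Sample Size and Power Considerations, choose one of two restatements:

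- 36 evaluable participants per group; allowing for 25% attrition, 96 participants are required (α .05, power .80, β .20); or
- keep 90 as the number that was planned, and state that at 25% attrition it gives about 77% power, with the assumptions named (two-sided .05, 1:1, 80% power at 36 per group). Correct the label to power .80 (β .20) here too.

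Changing the attrition assumption to 20% after enrolment has closed would make the numbers agree, but it would be a retrospective fit, so I would not do it.

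Bring the recruitment figure in the Abstract into line with the chosen text. Add one sentence linking Participant Timeline to Results that says when and why enrolment passed the planned 90. Leave the dated count of 90 in place if it is correct for its date.

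The cost is text only: no further participants and no change to the analysis.
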